**ENROLMENT:**						
**Eligibility screen**		X				
**Written or oral project information**		X				
**Informed consent**			X			
**Allocation**				X		
**INTERVENTIONS:**						
***LEAP***						
***TAU (both groups)***						
**ASSESSMENTS:**						
***BMI***	X^a^					
***ED diagnosis***	X^a^					
***EDE-Q***	X^a^				X	X
***CET***			X		X	X
***DERS***			X		X	X
***DSM-5***			X		X	X
***Active-Q***			X		X	X
***Treatment content questionnaire***						X
***Feasibility and accept. questionnaire***						X^b^
***SEDI***						X

^a^Part of standard assessment at treatment units at intake

^b^LEAP group only

##### Self-report and interview data

The project includes three assessment timepoints when participants complete questionnaires: T1, 3-month (T2) and 6-month follow-up (T3). Apart from the medical record data at T1, all measurements are distributed to participants through BASS (see below) after study consent. T1 includes self-reports CET, DERS, DSM-5, and Active-Q; T2 includes all T1 self-reports plus the EDE-Q; T3 includes all T2 self-reports plus the treatment content questionnaire (all) and LEAP feasibility and acceptance questionnaire (intervention group only). At T3, the SEDI is also performed by phone.

##### BASS Core Facility

The BASS Core Facility is a secure and encrypted tool for collecting questionnaire data online available through Karolinska Institute. Participants are directed to a secure registration procedure including double authorization with phone and e-mail, and consent to the study through Bank-ID. They also choose their own log-in details which are used subsequently. Each participant is assigned a patient ID used for all further pseudonymization. After study consent, BASS is used for all assessments, BASS manages the timing of later assessments; activation messages to participants and eventual reminders are sent automatically. BASS stores all item level survey data for each participant as soon as one entire instrument is completed; the entire assessment battery does not have to be completed for data to be saved. BASS also stores personal information obtained through the registration procedure (social security number, e-mail, phone number) and study consent, and several types of process data. The contact details are used to send automatic assessment activation messages and reminders. All project related data are stored within BASS for each participant at all timepoints as long as the project is active.

#### Participant retention

Participant retention is promoted by several strategies. Consenting and completing baseline measures through BASS is simple, works on several devices and can be completed at any time of the day. As few measures as possible are used so that assessments consume as little time as possible. Participants assigned to LEAP are given increased attention which is usually regarded as positive. It also begins with an individual session where the intervention is individually conceptualized, assumed to increase personal relevance and motivation. All participants are rewarded with gift cards after completed T2 and T3 assessments. A total of three reminders for late individual assessments are sent automatically every third day, all reminders include a link to BASS. Participants not responding to reminders will then be contacted by project managers. Retention in the LEAP intervention is managed locally at each unit.

#### Data management

*Personal data* (name, contact details) needed for study informing are stored locally at participating units in secure research registries. It is transferred regularly to project managers by phone and entered into a registry. *Medical record data* are transferred to project managers by phone, matched to the correct patient ID (created within BASS upon study consent) and entered into a separate dataset. *Recruitment and intervention data* (non-sensitive personal data (age, gender) for declining participants; intervention related process data) are stored locally at participating units in secure research registries and transferred to project managers after project termination. *Survey, interview, and assessment related data* are stored securely within BASS during the project time; only the project managers and BASS Data Base Administrator (DBA) have access to the database and activity within BASS is logged. After project completion, data will be exported into a separate dataset excluding personal data and deleted in BASS. *Overall project management data* are entered into a research registry at Karolinska Institute. Here, number of participants in each condition is entered as well as information on number of participants, dates, and LEAP therapists for each intervention group at participating units; no personal data are entered here. *Allocation information* including personal data and group is entered into a dataset by the AI and communicated to research contacts at each unit and the participants by phone. All these registries and datasets are stored on a secure server on Karolinska Institute (P-disc under DATA). After study completion, a pseudonymized master datafile will be compiled and stored on the secure KI server (P). A code key matching social security number and patient ID (retrieved from BASS) will be created and stored securely on an encrypted USB-stick in a fireproof safe separate from other data. All other registries containing personal data are destroyed. After project termination, the master datafile will be stored within the KI system for research documentation (ELN) along with the list of variables and related publications. Long-term storage of data follows the KI Archive Act.

#### Confidentiality

All data are kept confidential through the pseudonymized patient ID. During the project time, all project related data that can be connected to individual participants are stored securely at participating units and KI with limited access. The code key matching social security number and patient ID is encrypted and stored securely separate from other data. Analyses will only be performed in pseudonymized datasets.

#### Access to data (who has access to the full dataset)

Only the PI and PC have access to the registries kept during the project time on the secure KI server (P) (except allocation information). After project termination, only the PI and PC has access to the master datafile and code key. Selected data may be shared within the project group trough secure transfer for project related research. The PI determines the appropriateness of such research questions and only permits data access if they are clearly project related and covered by ethical permits.

### Statistical methods

#### Outcomes (methods for analyzing primary and secondary outcomes)

To evaluate the LEAP treatment effect (primary objective) the data will be analysed per protocol and based on intention to treat. The first analysis will include all controls (TAU) and participants that complete the program (LEAP+TAU) and answer the questionnaires. The T3 assessment point will be used for post treatment data unless the participants completed the program before T2. Each continuous outcome measure will be used as a response variable in a linear regression model with group allocation and baseline value as predictors. Logistic regression will be used for categorical outcomes. Additional covariates in the models will include gender, clinic, and time between T1 and first treatment session. Since the removal of drop out and noncompliant subjects in the per protocol analysis may lead to overestimation of the treatment effect, we will also perform the same analysis on the basic of intention to treat. Here all subjects who were randomized to LEAP and answered the questionnaires will be included in the treatment group, independently whether they participated in the LEAP sessions. Assessment points with at least CET and EDE-Q will be included in analyses in relation to the primary outcome. If data is missing on CET and/or EDE-Q, the timepoint will not be considered for analysis. There will be no item level missing data (technically prohibited in BASS). The percentage of patients withdrawing from the program despite the initial intention to participate will be considered as a feasibility marker. To compare proportions of dropout and loss to follow-up within the groups, conventional two-sample Z-tests will be used. To identify prognostic factors associated with a good response to LEAP (secondary objective), the treatment group will be subjected to additional analysis where the outcome of interest is used as response variable in linear or logistic regression model and potential prognostic factors (e.g., BMI, type of ED) are used as predictors. These analyses will include all participants with complete data for each specific model.

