#### Study design

The trial is a naturalistic two-armed parallel open-label superiority randomized efficacy trial, with recruitment from four Swedish specialist ED clinics. Eligible adult patients will be recruited via the clinics and randomized to treatment as usual (TAU) or TAU+LEAP, where LEAP will run in parallel with TAU. Key outcome variables in both arms are measured at initial assessment, after 3 months, and 6 months after initial assessment. Although most TAU+LEAP participants are expected complete the LEAP program prior to T2 assessment, a few may terminate LEAP prior to T3 (see Participant timeline).

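### The first-listed analysis sets LEAP completers against all controls, which tilts the estimate towards LEAP, and intention to treat is not named as the analysis that decides this superiority trial

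*Protocol article*

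**What the plan says.** Under Study design the trial is described as a "naturalistic two-armed parallel open-label superiority randomized efficacy trial".

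Under Statistical methods, Outcomes, the article says that for the primary objective "the data will be analysed per protocol and based on intention to treat". It then sets out the two analyses in this order:

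- **Per protocol.** "The first analysis will include all controls (TAU) and participants that complete the program (LEAP+TAU) and answer the questionnaires".
- **Intention to treat.** The article grants that "the removal of drop out and noncompliant subjects in the per protocol analysis may lead to overestimation of the treatment effect" and for that reason says "we will also perform the same analysis on the basic of intention to treat". In this set, "all subjects who were randomized to LEAP and answered the questionnaires will be included in the treatment group", whether or not they attended sessions.

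Both use the same model: regression of the outcome on group and baseline value, with further covariates. The article does not call either analysis primary, secondary or a sensitivity analysis, and does not say which one settles whether LEAP works.

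**The concern.** The completion filter acts on one arm. A LEAP patient who engages poorly or gets worse, and so does not finish, leaves the first analysis. A control with the same course stays in it. The groups being compared are then no longer the groups that were randomised.

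The article itself shows how prognosis can drive this selection. Under Modifications and discontinuation, a LEAP participant with, for example, severe psychiatric deterioration is discussed with the principal investigator, who may end the intervention. That patient has not completed the programme. No matching event removes a deteriorating control.

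A superiority claim could therefore rest on a non-randomised contrast that the authors already expect to be inflated. If the completer analysis is significant and the intention-to-treat analysis is not, nothing in the article says which conclusion the trial draws.

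**Working it through.** **Inputs from the article (Sample size).** Alpha .05, power .80 (written there as beta), effect size f = .25, pre-post correlation r = .50, 49 per arm required, 64 per arm enrolled, 30% drop-out. For two equal groups d = 2f = 0.5 SD.

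**The plan's own figure.** For a baseline-adjusted comparison the noncentrality is f²N/(1 − r²) = 0.0625 × 98/0.75 = 8.17. On 1 and 95 degrees of freedom the power is 0.808, so the required 98 reproduces. The planned effect of 0.5 SD and the residual factor √(1 − r²) = √0.75 are therefore sound benchmarks.

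**Assumptions not in the article.**
- A share p = 0.30 of LEAP patients do not complete. The 30% in the article is drop-out and is not stated to be programme non-completion; it only motivates the value.
- Non-completers do s = 0.25 to 0.5 SD worse than completers, with or without LEAP.

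**Bias with no LEAP effect.** Let completers have mean m. By randomisation the controls contain the same share p of patients who would not have completed, so their mean is m − p·s. The completer contrast therefore has expectation p·s instead of zero:
- 0.30 × 0.25 = 0.075 SD, and 0.075/0.5 = 15% of the planned effect;
- 0.30 × 0.50 = 0.15 SD, and 0.15/0.5 = 30% of the planned effect.

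**Type I error.** With 49 controls and 0.7 × 49 = 34.3 completers, SE = √0.75 × √(1/34.3 + 1/49) = 0.193. The two-sided rejection probability under no effect is Φ(−1.96 + bias/SE) + Φ(−1.96 − bias/SE).

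| Arm size | Bias (SD) | SE | Two-sided error | In favour of LEAP (nominal 2.5%) |
|---|---|---|---|---|
| 49 | 0.075 | 0.193 | 6.8% | 5.8% |
| 49 | 0.15 | 0.193 | 12.2% | 11.9% |
| 64 | 0.075 | 0.169 | 7.3% | 6.5% |
| 64 | 0.15 | 0.169 | 14.4% | 14.2% |

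**Simulation of the planned regression.** No LEAP effect, 64 per arm, 70% completion, 5,000 replicates per scenario. The assumed quantity is the correlation between the tendency to complete and the baseline-adjusted outcome.

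| Correlation | Bias, completers vs all controls (SD) | Type I error, completers vs all controls | Type I error, ITT with everyone analysed |
|---|---|---|---|
| 0 | 0.00 | 5.2% | 4.7% |
| 0.1 | 0.04 | 5.6% | 4.9% |
| 0.2 | 0.09 | 7.9% | 5.3% |
| 0.3 | 0.13 | 11.3% | 5.1% |
| 0.4 | 0.17 | 16.9% | 5.1% |
| 0.5 | 0.21 | 25.1% | 4.7% |

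Higher completion shrinks the problem. At correlation 0.3, 80% completion gives a bias of about 0.10 SD and an error of 9.2%; 90% completion gives about 0.05 SD and 5.2%. Repeating these two with 40,000 replicates gave 8.5% and 6.1%, so the differences are simulation noise.

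**The case against.** The strongest reply is that the article never calls the per-protocol analysis primary. The word first may only mean the first of two just named. Intention to treat is committed to in advance with the same model, and the direction of bias is disclosed. A reader would see both results, and an analysis plan not shown here might rank them. All of this mitigates the problem. It does not remove it: the populations and their order are stated here for the primary objective, and without a ranking either result can carry the conclusion.

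Second, in an add-on design controls have no programme to complete, and an efficacy trial may legitimately look at completers. That is true, but completers against all controls does not estimate efficacy in completers, because the controls who would have completed are not separated out. The naturalistic design, and the aim in the Discussion of national implementation, also point to the effect of offering LEAP.

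Third, the size rests on assumptions. This stands. With completion unrelated to outcome there is no bias, and with high completion or a weak link it is small. The article also describes its 49 as patients receiving LEAP, so taking a further 30% off is a scenario and not the article's own; using 64 per arm makes the inflation slightly larger.

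Fourth, the planned intention-to-treat set is itself limited to those who answered the questionnaires. If non-completers also stop responding, changing the order leaves part of the selection in place. This stands as a separate limit.

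**Conclusion.** The concern holds. The article lists first, for the primary objective of a superiority trial, a comparison filtered on completion in one arm only. It acknowledges the likely overestimation and does not make intention to treat decisive. The defect is that order together with the missing ranking; the article does not formally declare per protocol to be primary.

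With 30% non-completion and non-completers 0.25 to 0.5 SD worse off, the bias is 0.075 to 0.15 SD and two-sided type I error about 7 to 12%, nearly all of the excess in favour of LEAP. Across the simulated range at 70% completion the error runs from about 5% with no link between completion and outcome to 25% with a strong one, while intention to treat with everyone analysed stays near 5%. The direction is the one the article concedes; the size depends on completion and prognosis figures that it does not give. Because the trial's main claim depends on this choice, it should be settled before any outcome data are analysed.

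**What to change.** State that the primary analysis is by intention to treat, with all randomised patients in the arm assigned whatever their LEAP attendance, and that the trial's conclusion rests on it. Label the completers-against-all-controls analysis as supportive, with its expected direction of bias noted beside the result.

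If an effect in those who take up LEAP is wanted, estimate a complier-average causal effect with randomisation as the instrument, instead of deleting non-completers from one arm. If compliance means full completion, this assumes that partial attendance has no effect, and the plan should say so.

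The cost is reordering and wording: both arms are already scheduled for assessment at T2 and T3. The headline effect may be smaller. For example, if completers gained 0.5 SD, non-completers nothing, and 70% completed, the intention-to-treat effect would be 0.7 × 0.5 = 0.35 SD. The reordering does not by itself deal with randomised patients who do not answer the questionnaires; that needs its own missing-data provision.

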##### Primary research question

What are the treatment effects of LEAP on ED diagnosis, ED cognitions, CE behaviors and cognitions, BMI, emotion regulation and general psychopathology, after completion of the LEAP protocol.

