#### Interventions

The intervention group receive LEAP in addition to standard outpatient care (TAU) running in parallel, while the control group receive only TAU. Standard outpatient care includes a medical contact, psychoeducation about EDs, in most cases a CBT-based treatment via a personal therapeutic contact and/or group therapy, and meal-support. Everyone has a personalized treatment plan. There are no systematic interventions focusing on pathological exercise in TAU, which means that TAU+LEAP will clearly deviate from standard care.

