#### Participant timeline (Fig. 1)

Participants come to the clinic via clinical or self-referral. Within the first three visits, they are assessed using standardized diagnostic interviews, clinical rating scales, and self-report questionnaires. Eligible patients will be asked if they are interested in study participation by clinicians on participating units. Those who are interested will be contacted and formally recruited by the project manager or assistant. They are provided a link to BASS for study consent and the first assessment battery which can be completed directly. Afterwards, they are allocated to either control or intervention group. All participants continue TAU independent of group allocation; for those in the intervention group, LEAP starts when there are enough allocated patients (> 4 patients). After consent, study timeline is at minimum 182 days (three assessment points 90 days apart). Most participants in the intervention group will complete the LEAP program prior to T2 assessment, but due to variation in patient influx at units, some may instead terminate LEAP prior to T3. Participants are no longer included in the study after completed 6-month assessment (T3).

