#### Instruments/measures

##### Primary outcomes

Structured Eating Disorder Interview (SEDI [14];) is a semi-structured interview assessing ED diagnostic criteria according to DSM-IV. It is performed at T3; remission status (i.e., ED left or not) is used as outcome (binary data). The SEDI is also performed at three units at initial assessment to determine initial diagnosis. The SEDI has adequate psychometric properties [14]. The Eating Disorder Examination Questionnaire (EDE-Q [15];) is a 28-item questionnaire scored 0–6 (no days-all days) measuring severity of self-reported ED pathology the past 28 days. It generates an overall Global Scale and the subscales Restraint, Eating Concerns, Weight Concerns and Shape Concern. It also measures prevalence of ED behaviors such as restriction, binge-eating, purging and CE. This study will use information of presence and frequency of CE (binary and count data) and ED psychopathology scales as outcomes (continuous data). The EDE-Q has satisfactory psychometric properties [9, 16].The Compulsive Exercise Test (CET [17]; is a 24-item questionnaire scored 0–5 (never true-always true) measuring core psychological, behavioral, and emotional aspects of CE. It generates five subscales: Avoidance and rule-driven behavior, Weight control exercise, Mood improvement, Lack of exercise enjoyment, and Exercise rigidity. The LEAP treatment targets the aspects measured by the CET and all subscales are used as outcomes (continuous data). The CET has satisfactory psychometric properties [1, 17, 18].

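### As written, the rule for choosing the post-treatment assessment reads most LEAP patients at 3 months and controls at 6 months, so for EDE-Q, CET, DERS and DSM-5 symptoms arm is confounded with assessment time

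*Protocol article*

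**What the plan says.** The rule stands in the protocol article, Statistical methods, under Outcomes: "The T3 assessment point will be used for post treatment data unless the participants completed the program before T2". T3 is the default, and completing the program before T2 is the only exception.

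Four other parts of the article decide what the rule does:

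- **Who meets the exception.** Study design says that "most TAU+LEAP participants are expected complete the LEAP program prior to T2 assessment", and that "a few may terminate LEAP prior to T3". Participant timeline repeats the expectation: "Most participants in the intervention group will complete the LEAP program prior to T2 assessment".
- **Who cannot meet it.** Under Interventions, the intervention arm gets LEAP on top of TAU, "while the control group receive only TAU".
- **When outcomes are collected.** T2 is at 3 months and T3 at 6 months. EDE-Q, CET, DERS and the DSM-5 symptom measure are taken at both, in both arms. The SEDI remission interview and follow-up BMI are taken at T3 only.
- **What the model contains.** The terms are group, baseline value, gender, clinic and the wait from T1 to the first session. The intention-to-treat analysis is described as the same analysis on a wider set of patients.

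The primary research question asks for effects "after completion of the LEAP protocol".

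**The concern.** The time at which an outcome is read should not depend on the arm. Here it does, because the exception to T3 turns on an event that can occur in only one arm. Within the LEAP arm it also depends on something that happens after randomisation, namely whether and when the patient completes the program.

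TAU continues in both arms, so a control read at T3 has had about three more months of it than a LEAP patient read at T2. Any change over those months enters the group coefficient. That coefficient then estimates the LEAP effect neither at 3 months nor at 6 months. The sign is open: improvement under TAU between T2 and T3 would count against LEAP, while worsening under TAU, or a LEAP effect that fades after the program, would flatter it. A larger sample would not remove the problem.

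**Working it through.** **1. Who is read when, taking the rule literally**

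| Group | Completed before T2? | Time point | Per protocol | Intention to treat |
|---|---|---|---|---|
| LEAP, early completers (expected to be most) | yes | T2, 3 months | included | included |
| LEAP, late completers | no | T3, 6 months | included | included |
| LEAP, non-completers with data | no | T3, 6 months | excluded | included |
| Controls | no program to complete | T3 by default, 6 months | included | included |

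Both analyses therefore mix time points in the LEAP arm and set them against controls at T3.

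**2. Does a covariate repair it?** Baseline value, gender and clinic carry no information on assessment time. The wait from T1 to the first session is presented under Sample size as the variable time until a LEAP group starts. Controls have no such session, so this term cannot align the arms.

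**3. Which outcomes are exposed?** Those with data at both T2 and T3: EDE-Q, CET, DERS and DSM-5 symptoms. EDE-Q and CET carry ED psychopathology and pathological exercise, two of the three primary domains. SEDI remission and BMI have only a T3 follow-up reading, in both arms, so the rule cannot shift them.

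**4. The plan's own figure.** Inputs from Sample size: f = 0.25 (d = 0.5 for two equal groups), pre-post correlation 0.50, alpha 0.05, power 0.80, N = 98. For the between-groups F test with two measurements:

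λ = f² × N × m / (1 + (m − 1)ρ) = 0.0625 × 98 × 2 / 1.5 = 8.17, with 1 and 96 df, so power = 0.808.

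This reproduces N = 98. The planned model, with baseline as covariate, has the same noncentrality: λ = (N/4) × d² / (1 − ρ²) = 24.5 × 0.25 / 0.75 = 8.17.

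**5. Size of the bias.** Let p be the share of the analysed LEAP arm read at T2, δ the improvement under TAU from T2 to T3 in SD units, and τ₂ and τ₃ the LEAP effect at the two times. The expected contrast is

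p·τ₂ + (1 − p)·τ₃ − p·δ.

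If the LEAP effect is the same at both times, the bias is −p·δ. Measured against the T3 effect in general, it is p·(τ₂ − τ₃) − p·δ, which can take either sign.

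**6. Illustration.** The documents say only that p is most of the arm, and they give no δ. Assume p = 0.8, δ = 0.1 to 0.3, a constant effect of 0.5 SD and N = 98. The net effect is 0.5 − p·δ, and power comes from the noncentral F in step 4.

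| δ (SD) | Bias against LEAP | Net effect | λ | Power | Rejection rate if LEAP has no effect |
|---|---|---|---|---|---|
| 0 | 0 | 0.50 | 8.17 | 81% | 5% |
| 0.1 | 0.08 | 0.42 | 5.76 | 66% | 7% |
| 0.2 | 0.16 | 0.34 | 3.78 | 49% | 15% |
| 0.3 | 0.24 | 0.26 | 2.21 | 31% | 27% |

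The excess rejections in the last column are mostly in the wrong direction, favouring TAU. If p is varied from 0.6 to 0.9 over the same δ, the bias runs from 0.06 to 0.27 SD (12% to 54% of the planned 0.5) and power from about 70% down to 26%.

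**The case against.** The best defence is that the article nowhere states when controls are read. The rule follows directly on a sentence about controls and program completers, and the word participants may mean the completers alone. Matched or common timing for controls may have been intended. This stands in part: T3 for controls is what the literal rule produces, not an explicit statement, and a reader should not infer that the article declares it. It does not rescue the rule, because no reading supplies a common time point in words.

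A second defence is the aim. The research question concerns effects once the program is complete, so reading early finishers at T2 is understandable. That explains T2 for LEAP patients; it does not explain a later reading for their comparators.

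Several stronger readings are tempting, and the documents do not support them:

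- **That the whole comparison is affected.** Remission is a primary outcome, BMI is a secondary one, and both are read at T3 in each arm.
- **That the rule is known to work against LEAP.** TAU continues in both arms, but the article nowhere says that patients are expected to keep improving from month 3 to month 6.
- **That the intention-to-treat analysis separates attenders from non-attenders.** The rule turns on completion before T2, so partial attenders and late completers also go to T3.
- **That the benefit of randomisation is lost altogether.** The intention-to-treat groups are still formed by allocation. What differs is when their outcomes are read.

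**Conclusion.** The concern holds for outcomes measured at both T2 and T3. The stated rule ties assessment time to arm, the intention-to-treat analysis inherits it, and no model term corrects it. Two of the three primary domains are exposed; SEDI remission and BMI are not.

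The existence of the confounding rests on the wording of the rule and on the expectation that most LEAP patients finish before T2. Its size and direction rest on quantities the documents do not give. The illustrated loss of power, from 81% to between 66% and 31%, is conditional on an 80% share, 0.1 to 0.3 SD of TAU improvement and a constant LEAP effect, and should not be quoted as a property of this trial. The rule should be changed before analysis: it affects the main comparison, and the data for a common time point are already scheduled.

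**What to change.** Delete the switching rule and state that both arms are compared at the same prespecified time counted from T1, in the per-protocol and the intention-to-treat analyses alike. Either of these would do:

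- **T3 as primary in both arms, T2 in both arms as secondary.** T3 is the only follow-up shared by all outcomes, and the point by which LEAP is expected to be finished.
- **One mixed model** for each outcome measured at both times, with T2 and T3 from both arms, a group-by-time term and a named primary contrast.

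No new data collection is needed, but the choice is more than wording because it settles which effect is estimated. Assessments are 90 days apart, so with T3 as primary anyone who finished before T2 is read about three months or more after the program ends. By the article's own expectation that is most of the LEAP arm, and the result is then closer to a follow-up effect than to one measured right after completion. The T2 contrast in both arms should therefore be reported alongside it. If matched timing for controls was intended instead, the article must say so and define it.
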